## **Section 5: Trial Population**

### **Screening Data**

A selection of eligible people for the study will be invited from existing databases held at Academic Rheumatology, City Hospital Nottingham of participants with knee pain who have agreed to be contacted for future studies. Any shortfall in the recruitment will be compensated by sending study leaflet to GP surgeries.

## Eligibility

Potentially eligible people will be all men and women, aged between 45 years and older, registered with the GP surgery. The screening of existing records can be done by members of their direct healthcare team for those who had x-rays and osteoarthritis of the knee had been established. The GPs will follow the inclusion and exclusion criteria.

[figure not shown]

| INCLUSION CRITERIA                                                                                                                                                                                                                                                                                                                                                                                                                                                    | EXCLUSION CRITERIA                                                                                                                                                                                                                                                                                                                                                                                                                                                                                                                                                                                                                                                                                         |
|-----------------------------------------------------------------------------------------------------------------------------------------------------------------------------------------------------------------------------------------------------------------------------------------------------------------------------------------------------------------------------------------------------------------------------------------------------------------------|------------------------------------------------------------------------------------------------------------------------------------------------------------------------------------------------------------------------------------------------------------------------------------------------------------------------------------------------------------------------------------------------------------------------------------------------------------------------------------------------------------------------------------------------------------------------------------------------------------------------------------------------------------------------------------------------------------|
| 

•Aged 45 years and onward

•Clinical diagnosis of knee arthritis with complaints of knee pain for 3-6 months, early morning stiffness <30 minutes, crepitus, bony tenderness, and no palpable warmth and radiographically established osteoarthritis (at least score 1 on K/L scale)

•Able to read and write English

•Able to use/access computer or tablet and have access to the internet

 | 

•Inability to give informed consent

•Terminal or mental illness

•Neurological conditions (Stroke, Multiple Sclerosis, Parkinson's, Motor Neuron Disease, Muscular Dystrophy, Huntington's disease), inflammatory joint diseases including rheumatoid arthritis, gout or calcium pyrophosphate deposition disease (CPPD), and dementia

•Participants with sleep apnea previously diagnosed by a physician

•Acute soft tissue injury to the knee within last 3 months before recruiting diagnosed by a physician

•Unstable heart condition or rapid fluctuations in hypertension previously diagnosed by a physician

 |

[figure not shown]

## Recruitment

Recruitment will be presented as CONSORT flow diagram.

## Withdrawal / Follow-up

This will be presented in the article as per CONSORT guidelines. Loss to follow up will be presented as proportion of participants in each group not responding to the 6 week follow up survey.

## Baseline patient characteristics

**Descriptive baseline characteristics regarding age, sex, Body Mass Index (BMI) and Kellgren-Lawrence (KL) score will be presented for each group.**

**Sex will be presented as proportions (%). Age and BMI will be presented as mean (SD). KL score will be presented as median, mean (SD), and proportion in each category.**

## **Section 6: Analysis**

### **Outcome variables**

All outcome variables will be measured at baseline, and at follow up (after 6 weeks). The difference between baseline and follow up will be calculated and used as outcome measure in the analyses/group comparisons.

Primary outcome:  
NRS pain (0-10)

Secondary outcomes:

1. Sleep Quality: This was assessed by using actigraphy device known as ActTrust (53). A single device was given to each participant during baseline assessment session and was collected back during the follow-up session.
2. Pain sensitivity (Pressure pain thresholds – PPT, Temporal summation – TS, and conditional pain modulation – CPM).
3. Inflammatory markers on ultrasound (Synovial fluid, synovial hypertrophy and hyper vascularity) (MSK-USS)
4. Muscle Thickness Assessment (MTA) of Vastus Lateralis Oblique (VLO) using MSK-USS. This was dropped from the study due to lack of Panoramic view on Toshiba Aplio SSA-770A machine as the machine did not allow to find the mid-portion of the VLO to have valid and repeatable measurements.
5. Maximum Voluntary Contraction (MVC)- isokinetic contraction of Quadriceps and hamstring muscles using Computer Sports Medicine, Inc (CSMI) HUMAC / NORM Testing and Rehabilitation System (Model 770).
6. Physical functioning (Time up and go test, 30-second sit to stand test)
7. Western Ontario and McMaster Universities Osteoarthritis Index (WOMAC)
8. Pittsburgh Sleep Quality Index (PSQI)
9. General health questionnaire (MSK- HQ)

### **Analysis methods**

The distribution for each difference score will be evaluated. If the score follows an approximately normal distribution with no apparent outliers, between group differences will be analysed through ANOVA with adjustment for baseline scores (ANCOVA). Due to the randomisation, no systematic differences between groups are expected and hence no control for further “confounding” will be performed. Results for the between group comparison will be presented as “difference in mean difference” with accompanying 95% confidence intervals.

Within group differences from baseline to follow up will be evaluated through pre-post mean difference with accompanying 95% CI. Differences/changes with confidence intervals not covering “0” will be considered statistically significant. Standardised effect sizes (Cohen’s D) will be computed (mean difference/baseline SD).

If the difference scores clearly deviate from a normal/symmetric distribution, the comparisons will instead be performed through non-parametric analyses. For the

between group comparisons, Mann-Whitney test will be applied and for the within group comparison, Wilcoxon signed rank test will be used. Results will be presented as median scores (IQR) and p-values. No adjustment for baseline scores will be performed, as the non-parametric tests do not allow for this.

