## **Sample size and justification**

We are anticipating at least 60 individuals in each study arm at the closure of the study.

A recent systematic review of 44 high-quality exercise trials for knee OA pain (3537 participants) (106) found an average effect of 12/100 VAS points corresponding to 0.49 standard deviations. A sample size of n=60 per group is necessary to achieve 75% stat power. The estimated dropout rate for exercise interventions is 12%, therefore, a sample of 67 per arm will be recruited to achieve at least 75% power.

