### **Randomisation**

Participants will undergo computer-generated stratified randomisation by a statistician at Academic Rheumatology using the <https://sealedenvelope.com/> software. Generation of a randomisation schedule will include obtaining the random numbers and assigning random numbers to each subject under the specific treatment conditions. Participants will be equally allocated between treatment arms with at least n=67 per arm. As the online system will be used for randomisation, therefore, code break will be kept online, and the research manager will be responsible for keeping a track of it.

As per cohort multiple randomised controlled trial design mentioned by another study (54), individuals will have an assessment to establish their suitability for this study and once that has been established, we will randomise them into control group and interventional group. At this occasion, individuals will find out that they belong to one group or the other and hence blinding is not possible. Because the lack of masking might affect the motivation of participants randomised into the control arm, individuals in the control arm will be offered access to the web-based exercise programme after the six weeks of the study, if they wish to use it to avoid a placebo effect in this group. Blinding such interventional studies are difficult to achieve as participants will establish as to in which group they are in, however, the examiner will be blinded to the intervention.

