## **Sample size**

The sample size calculation is based on a standardised effect size of 0.49, corresponding to a group difference in primary outcome VAS pain of 12 points on a scale of 0-100 (corresponding to a mean difference of 1,2 points on a 1-10 NRS scale). This difference was found in a recent systematic review of 44 high-quality exercise trials for knee OA pain (3537 participants) (56). With this estimated effect, 60 participants in each group is required to achieve 75% power to reject the null hypothesis, with alpha level set to 0.05.

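### Randomisation is described as stratified, but the primary ANCOVA leaves the strata out, for a reason that does not address variance

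*Combined protocol and SAP*

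**What the plan says.** The protocol (Randomization and Blinding) and the SAP (Section 3, Randomisation) use the same sentence: "Participants will undergo computer-generated stratified randomisation by a statistician at Academic Rheumatology". The text that follows describes the schedule only in general terms: "Generation of a randomisation schedule will include obtaining the random numbers and assigning random numbers to each subject under the specific treatment conditions". Neither document names a stratification factor, a number of strata or a block size.

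The SAP (Section 6, Analysis methods) compares arms on the change from baseline by ANCOVA, with the baseline score as the only covariate. It then excludes anything else: "Due to the randomisation, no systematic differences between groups are expected and hence no control for further" confounding. If the change scores are clearly non-normal, the comparison becomes a Mann-Whitney test: "No adjustment for baseline scores will be performed, as the non-parametric tests do not allow for this". No section puts the strata in any model or explains why they are omitted.

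**The concern.** The analysis does not follow the design as described, and the reason given answers a different question. Randomisation does remove systematic differences, so omitting strata does not bias the comparison. The issue is variance. When arms are balanced within prognostic strata, the treatment estimate varies less from trial to trial. A model without the strata leaves their variance in the residual and so does not report that gain.

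What could be at stake is an interval for NRS pain that is wider than the design warrants, and a test that runs below 5%. The plan aimed for only 75% power with 60 per group, and the SAP reports 105 participants completing both visits. Precision that can be reported without new data is worth having here.

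**Working it through.** **The plan's own figure.** The SAP states: "The sample size calculation is based on a standardised effect size of 0.49". The protocol gives the source: the review "found an average effect of 12/100 VAS points corresponding to 0.49 standard deviations", so the implied SD is 12/0.49 = 24.5 VAS points. Alpha is 0.05, with sidedness not stated. Two-sided:

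- n per arm = 2 × (1.960 + 0.674)² / 0.49² = 57.8, so 58.
- Power at 60 per arm = Φ(0.49/√(2/60) − 1.96) = Φ(0.724) = 76.5% (75.9% by noncentral t).

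The stated 60 per group for 75% power is reproduced. One-sided 0.05 gives 45 and does not reproduce it. Stratification plays no part in this calculation, so the sample size is not made wrong by this point.

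**Assumed inputs.** R² is the share of variance remaining after the baseline score that the strata explain. The documents do not give it; the range 0 to 0.20 is an assumption. Arms are assumed to be balanced within strata. The 105 completers are assumed to split equally (52.5 per arm), and the correlation of follow-up with baseline pain is assumed to be 0.5. No outcomes are imputed.

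**Formulae.**

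- Reported SE / true SE = 1/√(1 − R²)
- Type I error of the baseline-only model = 2Φ(−1.96/√(1 − R²))
- Residual SD after baseline = √(1 − 0.5²) = 0.866, so SE = 0.866 × √(2/52.5) = 0.169 and λ = 0.49/0.169 = 2.90
- Power, baseline-only = Φ((λ − 1.96)/√(1 − R²))
- Power, with strata = Φ(λ/√(1 − R²) − 1.96)

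| R² | SE too large by | Type I error | Power, baseline-only | Power, with strata | Loss (points) |
|---|---|---|---|---|---|
| 0 | 0% | 5.0% | 82.6% | 82.6% | 0 |
| 0.05 | 2.6% | 4.4% | 83.2% | 84.5% | about 1 |
| 0.10 | 5.4% | 3.9% | 83.9% | 86.3% | about 2.5 |
| 0.20 | 11.8% | 2.8% | 85.3% | 90.0% | about 5 |

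Both power columns use the normal approximation, which ignores the degrees of freedom spent on strata. If 0.49 is instead taken as the effect in residual SD units, with no credit for the baseline correlation, λ = 0.49/√(2/52.5) = 2.51. Power is then 71.4% against 73.1%, 71.9% against 75.4%, and 73.1% against 80.2% for the three non-zero rows, a loss of about 2, 3.5 and 7 points.

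**Simulation check.** The settings were 120 participants, four strata, 6,000 replicates, R² = 0.10 and an effect of 0.49 residual SD.

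- *Permuted blocks of four within strata.* The baseline-only model SE was 0.183, against an empirical SE of about 0.176. Type I error was 4.4% (Monte Carlo error about 0.3 points). Power was 75.6% without strata and 78.9% with them. The empirical SE of the estimate was nearly the same either way (0.1755 and 0.1752).
- *Simple randomisation.* The baseline-only SE was about right (0.184 against 0.187 empirical), with type I error 5.5%. Adjusting for the strata still raised power, from 74.7% to 77.7%.

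**The case against.** A reader might infer from the word stratified that the NRS interval is certainly too wide and the test certainly below 5%. The documents do not support that, for three reasons.

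- **Balance within strata is not described.** The schedule text mentions random numbers and equal arms, but no blocking. Without balance inside strata, the baseline-only standard error is correct, as the simple-randomisation result shows.
- **No factor is named.** If the factors do not predict pain change, nothing is lost. If the factor is baseline pain, the ANCOVA already carries most of it.
- **Missing data act the other way.** The SAP analyses by intention to treat and fills gaps by group mean imputation, which shrinks reported standard errors. In a simulation with blocked strata, baseline correlation 0.5, 120 participants and 12% of outcomes replaced by the arm mean, type I error of the baseline-only model was about 8%, 7% and 6% at R² = 0.05, 0.10 and 0.20. The 12% is the protocol's dropout estimate; the number actually imputed is not stated. The net direction can therefore reverse.

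It would also be too strong to say that precision is thrown away under a blocked design. The estimate itself is equally precise with or without strata; only its reported standard error is too large.

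These objections make the consequence conditional. They do not remove the mismatch. Both documents call the design stratified, the analysis rules the strata out, and the stated reason concerns bias only.

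**Conclusion.** The point holds as a mismatch between design and analysis, with a conditional and moderate consequence. The figures in the table apply only if allocation is balanced within strata and the strata explain the assumed share of residual variance, and only before imputation. At R² = 0 there is no loss. Where the effect exists it is conservative, so the validity of a positive finding is not threatened by this point alone.

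The size cannot be narrowed further, because the factors and blocking are not stated. For the same reason, a strata-adjusted analysis cannot be specified from the documents as they stand. The change is worth making because it costs almost nothing in a trial that fell short of its planned numbers.

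**What to change.** In the SAP (Section 6, Analysis methods), replace the sentence that excludes further control with: *The ANCOVA includes arm, baseline score and the stratification factors used in the randomisation schedule as fixed effects.* Name those factors, their levels and any blocking there and in both randomisation sections. Take them from the schedule actually used, not from inspection of the outcome data. If a factor is left out, give a reason that addresses variance. If the schedule was not in fact stratified, correct both documents instead.

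Where the non-parametric fallback applies, replace the Mann-Whitney test with a stratified rank test (van Elteren), since Mann-Whitney cannot take the strata.

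Group mean imputation uses no model to which the strata could be added, so this point asks for no change there; its effect on standard errors is a separate matter. The cost is SAP wording and a few degrees of freedom (levels minus one for each factor). No new outcome data are needed.

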## **Section 4: Statistical Principles**

### **Confidence intervals and p-values**

Alpha level will be set to 0.05. 95% confidence intervals will be presented (if data allows for parametric analyses).

Adjustments for multiplicity will not be performed. However, primary outcome is defined and will be the main focus for the results interpretation. Remaining analyses will be considered exploratory, and interpreted in light of the general pattern of effects rather than solely based on individual p-values.

Adherence to the i-BEAT OA will be defined as percentage patient completed activities of those distributed by the platform per week. Number of non-compliant participants will be reported.

Analyses will be based on the Intention to treat (ITT) population. Since there are no risks associated with i-BEAT OA, safety analyses will not be performed.

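### When change scores are judged non-normal or asymmetric, the SAP's within-arm result becomes a Wilcoxon signed rank p-value beside a median with no interval, and with skewed changes that p-value does not test the median change

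*Combined protocol and SAP*

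**What the plan says.** Section 6 of the SAP (Outcome variables) makes the change from baseline to six weeks the analysed quantity for every outcome. Under Analysis methods the choice of technique depends on a look at the data: "The distribution for each difference score will be evaluated".

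- **Parametric branch** (approximately normal changes, no apparent outliers). Between arms the analysis is ANCOVA. Within arms, "Within group differences from baseline to follow up will be evaluated through pre-post mean difference with accompanying 95% CI".
- **Fallback branch.** "If the difference scores clearly deviate from a normal/symmetric distribution, the comparisons will instead be performed through non-parametric analyses". Between arms this means Mann-Whitney; "for the within group comparison, Wilcoxon signed rank test will be used". The output is then described as follows: "Results will be presented as median scores (IQR) and p-values".

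For the fallback branch the SAP gives no within-arm null hypothesis, symmetry condition, estimate matched to the signed rank test, or interval. It does not say whether the medians are of changes or of the scores at each visit, or whether the distribution is checked per arm or pooled.

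**The concern.** The signed rank test addresses the median change only if the paired changes are symmetric about their centre. A rule that reaches this test because symmetry has been judged to fail will, in those cases, print a p-value for one quantity beside an estimate of another. A reader will naturally take the p-value as a test of the median next to it.

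Two things are at stake. A skewed outcome could be reported as a significant within-arm change although the typical participant did not change. The reader also loses the interval that the parametric branch would have given. The rule applies to the within-arm result for NRS pain and every secondary outcome, in both arms.

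**Working it through.** **Step 1: the plan's own figure.** The only design calculation in the SAP is this: "The sample size calculation is based on a standardised effect size of 0.49", so that "60 participants in each group is required to achieve 75% power to reject the null hypothesis, with alpha level set to 0.05". Taking alpha as two-sided (the SAP does not say):

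- n per arm = 2(1.960 + 0.674)² / 0.49² = 57.8, so 58 (59 with the t distribution).
- Power at 60 per arm = Φ(0.49 × √(60/2) − 1.960) = Φ(0.724) = 76.5% (75.9% with the t distribution).

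The stated figure reproduces. The present point neither disputes it nor depends on it.

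**Step 2: inputs for the check.**

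- Level: "Alpha level will be set to 0.05" (SAP Section 4), two-sided assumed.
- Sample: 105 participants completed both visits (SAP, Timing of outcome assessments). 105 / 2 = 52.5, so about 52 per arm; the split is an assumption. 60 and 67 per arm, the planned figures, were also run.
- Shape of the changes: not in the documents, so a range is assumed.

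**Step 3: what the signed rank test targets.** It is centred on the pseudomedian, the median of (D₁ + D₂)/2 for two independent changes. Under symmetry this equals the median and the mean; under skewness the three separate. Take exponential changes (SD 1, skewness 2):

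- median = ln 2 = 0.693, and mean = 1;
- the pseudomedian x solves (1 + 2x)e^(−2x) = 0.5, giving x = 0.839.

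If the true median change is set to 0, the pseudomedian is 0.839 − 0.693 = 0.146 SD and the mean is 1 − 0.693 = 0.307 SD. The signed rank test therefore has something to detect although the median has not moved.

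**Step 4: rejection rates at n = 52** (nominal 5%, 4,000 runs per row, zero changes dropped from the Wilcoxon test, Monte Carlo SE below 1 percentage point).

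| Change distribution (assumed) | Skewness | True value at 0 | Wilcoxon | Sign test | t test |
|---|---|---|---|---|---|
| Normal | 0 | median and mean | 4.7% | 3.4% | 5.0% |
| Gamma, shape 4 | 1 | median | 8.3% | 3.5% | 18.1% |
| Exponential | 2 | median | 21.2% | 3.7% | 59.4% |
| Integer NRS change, 35% better, 35% worse, 30% unchanged | −0.84 | median | 23.9% | 4.0% | 28.4% |
| Gamma, shape 4 | 1 | mean | 10.0% | 14.2% | 5.9% |
| Exponential | 2 | mean | 23.5% | 43.3% | 6.6% |

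Independent repeats of the gamma and exponential rows with median 0 gave Wilcoxon rates of 8.5% to 8.6% and 21.3% to 22%. The sign test sits below 5% because it is discrete: for 52 non-zero changes its exact level is 2 × P(Bin(52, 0.5) ≤ 18) = 3.6%. In the integer NRS row the mean does improve, so that row shows only that the test is not one of the median.

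**Step 5: other shapes and sizes** (10,000 runs each, n = 52, 60 and 67, true median change 0). Wilcoxon rejects 12.8% to 15.8% for chi-square with 4 df, 21.3% to 28.1% for exponential, 11.3% to 14.0% for lognormal with σ = 0.5, and 25.7% to 31.9% for lognormal with σ = 1. The rate rises with n, so a larger sample does not cure the mismatch. The exact sign test stays between 2.6% and 5.4% throughout.

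**Step 6: where the planned test is sound.** For normal and heavy-tailed symmetric changes (t with 3 df) Wilcoxon rejects 4.7% to 5.0%. For exchangeable pre and post scores with skewed marginals it rejects 4.7% to 5.3%.

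**The case against.** A reader might infer that the signed rank test is invalid whenever the SAP uses it. The documents do not support that, for two reasons.

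- The trigger is worded loosely. The parametric branch requires near-normality and no apparent outliers, and the fallback refers to departure from a normal or symmetric shape. A symmetric outcome with heavy tails or outliers could plausibly land in the fallback, and there the test holds its level.
- The SAP does not state the within-arm null. If it is that pre and post scores are exchangeable, changes are symmetric in the population and the test is valid. Selecting samples that merely look non-normal does little harm. Among exchangeable data sets picked out by a Shapiro test at 0.05, rejection was 4.7% to 5.9%. With a trigger of absolute skewness above 0.8 it was 5.1% and 5.9% for two shapes. A third, NRS-like shape gave 12.5%, but on only 72 triggering samples, which is too few to rely on.

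A reader might also infer that the discarded mean interval is simply the better analysis. The table does not show that. With the true median at zero, the t test rejects more often than Wilcoxon in all three skewed rows (18.1% against 8.3%, 59.4% against 21.2%, 28.4% against 23.9%). With the true mean at zero, the sign test rejects more often than Wilcoxon. Each procedure answers its own question. The t interval is close to nominal for the mean under moderate skew (5.2% to 6.6%) but not under extreme skew (9.4% to 9.9% for lognormal, σ = 1). Nor does the fallback list a mean, so a mismatch with a displayed mean cannot be charged to it.

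Finally, the trial's hypothesis is superiority to usual care (SAP, Framework), a between-arm question. Section 4 treats analyses other than the primary outcome as exploratory, to be read by their overall pattern.

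All of this stands, and it limits the point without removing it. The trigger expressly covers clearly asymmetric changes. In those cases the SAP shows a median, gives no interval, and attaches a p-value that does not test that median. If the medians are of visit scores and not of changes, the p-value is no closer to what is displayed.

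**Conclusion.** The concern holds as a mismatch between p-value and reported estimate in one branch of the within-arm analysis. With about 52 per arm and a true median change of zero, the rate of nominally significant results is roughly 8% at skewness 1 and 22% at skewness 2, instead of 5%. These sizes rest on assumed skewness, an assumed near-equal split of the 105 completers and a two-sided 5% level. With symmetric changes there is no inflation.

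The between-arm comparison and the sample size are unaffected by this point. Severity is minor to moderate: worth correcting because the rule is explicit, removes the interval and covers every outcome, but not a threat to the trial's main conclusion.

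**What to change.** Amend the fallback paragraph under Analysis methods in SAP Section 6:

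1. For every outcome, report the within-arm mean change with its 95% CI whatever the shape, using a bootstrap interval if the changes are skewed.
2. If a median is also shown, make it the median change and give its order-statistic (sign-test) 95% CI.
3. If the signed rank test is kept, pair it with the Hodges-Lehmann pseudomedian and its CI, and describe it as such and not as a test of the median.

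Item 3 alone would repair the match between p-value and estimate for anyone who prefers to keep the planned test. The cost is a few sentences of SAP text and a few lines of code, with no new data. The downside is that the order-statistic interval for a median is somewhat wider than a signed-rank-based interval.

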|---------------------|--------------------------------------------------------------------------------------------------------------------------------------------------------------------------------------------------------------------------------------------------------------------------------------------------------------------------------------|
|                     | Pain (Pressure pain threshold – PPT, Temporal summation – TS, and conditional pain modulation – CPM)
Muscle Strength - Dynamometer
Physical functioning (Time up and go test, 30-second sit to stand test)
Western Ontario and McMaster Universities Osteoarthritis Index (WOMAC)
General health questionnaire (MSK- HQ) |
| Statistical methods | Standard parametric regression methods will be used to assess the effect of exercise on pain sensitivity, pain scores, and sleep patterns                                                                                                                                                                                            |

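### The SAP picks the primary test by an undefined look at the change scores, and its fallback gives up both baseline adjustment and a between-group estimate with confidence interval

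*Combined protocol and SAP*

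**What the plan says.** SAP Section 6 (Outcome variables) makes the change from baseline to six weeks the analysed quantity for every outcome, including the primary, NRS pain. Analysis methods then sets a two-branch rule. The first branch reads: "If the score follows an approximately normal distribution with no apparent outliers, between group differences will be analysed through ANOVA with adjustment for baseline scores". It is reported as a difference in mean change with a 95% interval. If the change scores depart clearly from a normal or symmetric shape, the comparison becomes a Mann-Whitney test, reported as medians with interquartile range and p-values, and "No adjustment for baseline scores will be performed, as the non-parametric tests do not allow for this".

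SAP Section 4 makes the interval conditional in the same way: "95% confidence intervals will be presented (if data allows for parametric analyses". The protocol synopsis has no such switch: "Standard parametric regression methods will be used to assess the effect of exercise".

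The same SAP paragraph evaluates within-arm changes and calls them statistically significant when the interval excludes zero. SAP Section 3 (Timing of outcome assessments) reports that the trial stopped on 19 March 2020 with 105 participants completing both visits.

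**The concern.** The primary test of a superiority trial should be fixed before anyone can see which choice helps. Here it turns on a visual judgement with no stated test, cut-off, blinding or responsible person, in a document written after data collection had stopped. The two conditions also do not cover every case: a broadly symmetric change score with one visible outlier fails the first without clearly meeting the second.

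Three things are at stake:

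- **Estimate.** Under the fallback, no between-group effect with an interval is reported, so the result cannot be compared with the 1.2-point difference behind the sample size.
- **Precision.** Unadjusted change scores generally carry more variance than a baseline-adjusted comparison, and the trial has 105 completers against 120 planned evaluable at 75% power.
- **Interpretation.** Significance labels on within-arm changes sit beside the between-group result, although they do not test superiority over usual care (SAP, Framework).

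**Working it through.** **1. The plan's own figure.** Inputs from SAP, Sample size: "standardised effect size of 0.49, corresponding to a group difference in primary outcome VAS pain of 12 points on a scale of 0-100"; "60 participants in each group is required to achieve 75% power to reject the null hypothesis"; "with alpha level set to 0.05". Sidedness is not stated. Two-sided is assumed because it reproduces the plan (one-sided gives 45 per arm).

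- n per arm = 2(1.960 + 0.674)² / 0.49² = 58 (59 with the t distribution), against 60 stated.
- Power at 60 per arm = Φ(0.49 × √30 − 1.960) = 76.5% (75.9% with t), against 75% stated.

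The figure reproduces. Implied SD: 12/0.49 = 24.5 on 0-100, or 2.45 on 0-10.

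**2. Power of each branch, normal theory.** Assumed: 52.5 per arm (105 completers; the split is not given), 0.49 in units of the score SD, and baseline to follow-up correlation ρ of 0.3 to 0.7 (not given in the documents).

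- ANCOVA: Φ(0.49 √(52.5/2) / √(1−ρ²) − 1.960)
- Mann-Whitney on change: Φ(0.49 √(52.5/2 × 3/π) / √(2(1−ρ)) − 1.960), where 3/π is its efficiency relative to the t test under normality.

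| ρ | ANCOVA | Mann-Whitney | Loss (points) |
|---|---|---|---|
| 0.3 | 74.9% | 54.5% | 20.4 |
| 0.4 | 78.2% | 61.0% | 17.2 |
| 0.5 | 82.6% | 68.9% | 13.7 |
| 0.6 | 88.1% | 78.3% | 9.7 |
| 0.7 | 94.0% | 88.6% | 5.4 |

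(Losses are taken before rounding.) The SAP does not say whether 0.49 refers to the SD of the score or of the change. If it is the change, the losses over the same ρ are 18.7, 16.2, 13.7, 11.2 and 8.8 points.

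**3. Simulation, because the fallback is meant for non-normal data.** 6,000 trials per cell, 53 v 52, effect 0.49 SD. Cells show power (%) as ANCOVA / Mann-Whitney on change / baseline-adjusted rank ANCOVA.

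| ρ | Rounded 0-10 NRS, normal residuals | Unbounded, heavy-tailed (t, 3 df) | Unbounded, skewed (exponential) |
|---|---|---|---|
| 0.3 | 71.6 / 51.9 / 70.0 | 77.3 / 66.0 / 91.9 | 74.2 / 64.3 / 91.9 |
| 0.4 | 75.6 / 58.1 / 73.5 | 80.2 / 73.8 / 92.6 | 77.9 / 72.2 / 92.0 |
| 0.5 | 80.3 / 65.2 / 78.5 | 83.4 / 82.7 / 93.8 | 81.6 / 81.1 / 92.7 |
| 0.6 | 85.0 / 74.8 / 82.9 | 88.6 / 91.5 / 95.9 | 87.4 / 89.9 / 93.9 |

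On the unbounded scale ANCOVA's advantage shrinks as ρ rises and reverses by up to about 3 points. With the scale rounded and cut at 0 and 10 (SD 2.45, effect 1.2, ρ 0.3 to 0.7), the fallback loses about 7 to 21 points with normal residuals. With heavy-tailed or skewed residuals it runs from about 21 lost to about 2 gained. Rank ANCOVA beats Mann-Whitney in every cell above and is not materially below it on the bounded scale.

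**4. Type I error.** ANCOVA on the bounded scale stays at 4.1 to 5.6%, including non-normal residuals. A fixed Shapiro-Wilk rule (assumed; the SAP names no test) gave 5.0 to 5.4% at ρ = 0.5. Taking whichever p-value is smaller gave 7.0 to 8.3% in those runs, and about 6 to 8% across all simulations.

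**5. How often the switch happens.** For rounded NRS data with normal residuals at ρ = 0.5, the answer depends on the rule one invents:

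- Shapiro-Wilk on arm-centred changes: 22.5%
- Shapiro-Wilk in either arm: 40 to 45%
- Shapiro-Wilk on pooled changes: 56 to 68%
- Pooled absolute skewness above 0.5: about 3%
- Any value beyond 3 SD: 20 to 23%

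**6. Within-arm labels.** If both arms improve equally, the chance that exactly one is labelled significant is 2p(1−p), where p is the within-arm power. With 52 per arm and a change of 0.3 SD, p = 0.565 and 2 × 0.565 × 0.435 = 49%. This is near the formula's ceiling of 50%. It is 19% at 0.1 SD, 31% at 0.4, 11% at 0.5 and 2% at 0.6.

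**The case against.** The default is already the right one: baseline-adjusted ANCOVA with a 95% interval. Both branches are written down, one primary outcome is named, and the fallback is reserved for clear departures from normality. In such data Mann-Whitney can match or slightly beat ANCOVA. The stated reason is also true of the two tests named, since neither Mann-Whitney nor Wilcoxon takes a covariate. A fixed two-stage rule barely moves the type I error, and the SAP does not permit taking the smaller p-value.

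Most of this stands, and it limits the point. A reader might infer that the switch is likely because an integer scale is never exactly normal. The SAP asks only for approximate normality of the change score, and section 5 of the working shows no rate can be assigned. A reader might also infer that the test was chosen after seeing results by arm. The SAP shows that the trial had stopped, not that anyone had looked. Nor are within-arm results offered as the superiority test, since a between-group comparison is specified separately.

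What the objection does not answer is the missing criterion and the loss of an estimate with interval. Where a rank method is warranted, a baseline-adjusted one is available and performs at least about as well as the fallback. Even Mann-Whitney can be accompanied by an interval for the location shift.

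**Conclusion.** The point holds as a fault in specification. The primary test rests on an undefined inspection, and the fallback drops baseline adjustment and the between-group interval for a reason that is incomplete rather than wrong.

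The power cost is a range under assumptions: ρ of 0.3 to 0.7, SD 2.45, effect 1.2 and 105 completers split about evenly. It is about 7 to 21 points with normal residuals, and from about 21 lost to about 2 gained with heavy-tailed or skewed ones. A single figure of about 14 to 16 points, which one gets near ρ = 0.5 with near-normal data, is not supported as the cost of the SAP's rule. The documents give no correlation, and that figure compares always using one test with always using the other. The switch offers no visible protection, because ANCOVA's type I error stays near 5%. The risk of inflation to about 6 to 8% arises only if the open wording is used to choose the smaller p-value. Severity: should be fixed.

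**What to change.** In SAP Section 6, make ANCOVA of NRS pain with baseline as covariate the primary analysis whatever the distribution of the change score. Always report the adjusted mean difference with its 95% interval, using a robust or bootstrap interval if the residuals are non-normal. Name one sensitivity analysis that keeps the baseline: rank ANCOVA or proportional-odds regression. Remove the Mann-Whitney branch and the sentence that justifies it, and delete the condition on intervals in SAP Section 4. Report within-arm changes as description, without significance labels or signed-rank p-values. Record the date of the change and whether anyone had seen outcomes by arm.

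The cost is wording only, with no new data. The downside is that a mean difference is reported even when change scores are skewed. With strongly heavy-tailed or skewed residuals the rank analysis may also be the more powerful of the two, which is why it should be named in advance and reported alongside.
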